### Interventions

All eligible patients will be randomized into two groups as follows:YPF treatment group: YPF 5 g per time, three times daily, for 52 weeks.Control group: placebo 5 g per time, three times daily, for 52 weeks.

YPF and placebo are uniformly supplied by Sinopharm Group Guangdong Medi-World Pharmaceutical Co., Ltd (Foshan, Guangdong Province, China). The experimental drugs, which have an identical appearance and almost similar taste, are manufactured according to the requirements of this clinical trial and meet the relevant quality requirements. YPF granules have been on the market for many years and there are clear standards for prescription, dosage and quality control. Details can be found in the 2020 edition of the Pharmacopoeia of the People’s Republic of China (hereafter referred to as the 2020 Chinese Pharmacopoeia). The placebo formulation consisted mainly of dextrin and mannitol (66.1% and 30.4% of the placebo, respectively). A small amount of 5% YPF extractum (2% of the placebo) was added to make the odour essentially identical to that of YPF. At the same time, a small amount of flavoring agents and food coloring was added to make the taste and appearance of the placebo similar to that of YPF.

Based on the clinical symptoms, signs and the GOLD guideline 2021, all patients in both groups will receive routine therapy (taking the commonly used maintenance medications in COPD, such as ICS/LABA/LAMA, theophylline, roflumilast, etc.) without intervention, but detailed medication should be recorded for summary analysis. At the same time, the medications (or other treatments) that have to be continually taken continuously for the underlying diseases, the dosage, frequency, and duration of use should also be recorded in the case report form (CRF). It’s forbidden to take other Traditional Chinese medicines or proprietary Chinese medicines with the same effect as YPF during the trial.

### Randomization, blinding and unblinding

The Interactive Web Response System (IWRS) will be used in this study. We will perform stratified block randomization for the eligible subjects, the absolute value of eosinophils in peripheral blood at the time of enrollment is taken as the stratification factor, and the cut-off value of the absolute value of eosinophils is set at 0.3 × 10^9^/L. The SAS 9.4 is used to generate the random number table and the drug random number table. Based on the two random number tables, the subjects are randomly divided into the YPF group and the control group. The administrator of IWRS will send the account number and password to the designated person in charge of each centre before the study. Then the investigator will log into the IWRS and enter the relevant information of the subject. The subject will be assigned a unique random number, which will be displayed by the IWRS.

In the trial, investigators, subjects, supervisors and clinical research coordinators will remain blinded. All experimental drugs and placebos are packaged in a uniform manner, with no difference in appearance, and blinded according to the drug random number table by people independent of the study. Investigators and subjects only know the random number and the drug number, and don’t know the treatment regimen represented by these random numbers.

Unblinding requirements: After all data have been entered into the Electronic Data Capture (EDC) system, the database is locked through a process of query, verification, and blinding review. The principal investigators and statisticians will then unblind the data and distinguish the groups of the subjects and corresponding interventions. The assessors then perform the statistical analysis after the data are unblinded. In case of an emergency (such as serious adverse events, serious complications, etc.) and the need for rescue measures, unblinding can be done urgently with the identification and signature of the principal investigator. The sponsor and the principal investigator should be notified within 24 h of the emergency unblinding, and the reason for the emergency unblinding should be explained. The rate of emergency unblinding should not exceed 20%, otherwise, the study may be considered a failure. Unblinding should not be performed in cases of withdrawal for therapeutic reasons.

### Outcome measurements

#### Efficacy indicators

The primary outcome is the changes in the COPD assessment test (CAT) score after 52-week of treatment. Specifically, the differences between the total CAT score at week 52 and baseline will be calculated respectively for the experimental and the control groups, respectively, and the difference between the two groups will be compared. The secondary outcomes include the following eleven indicators:Annualized rates of moderate or severe COPD exacerbations. The measure is the number of acute exacerbations of moderate or severe COPD during 52-week treatment/total participants in the group. The definition of an acute exacerbation of COPD (AECOPD): is an acute change in a patient’s baseline dyspnea, cough, and/or sputum beyond day-to-day variability sufficient to warrant a change in therapy. The severity of AECOPD is graded as follows: (1) Mild: requires only increased treatment with short-acting bronchodilators, such as short-acting β-receptor agonists (SABA); (2) Moderate: requires increased antibiotics and/or oral glucocorticoid hormone; (3) Severe: requires hospitalization or emergency treatment, may be complicated by acute respiratory failure.All-cause admission rate and admission rate due to acute exacerbation. All-cause admission rate = (total number of admission during 52-week treatment)/ (total number of participants in the group) and the admission rate due to acute exacerbation = (number of admission due to acute exacerbation during 52-week treatment)/ (total number of participants in the group).The changes in the St George's Respiratory Questionnaire (SGRQ) score.The proportion of patients with an SGRQ response (defined as an improvement of ≥ 4 units from baseline).The changes in the CAT score.The median time to the first exacerbation of COPD and the median time to the first exacerbation of moderate or severe COPD during treatment.Duration and time interval of acute exacerbations compared with the control group.Annualized rates of acute exacerbations of COPD of different severity.The changes in clinical symptom score (Table 2) compared with the control group.The changes in the individual clinical symptom score compared with the control group.Frequency of first-aid drug use.The changes in TCM constitution from the baseline to week 24 and week 52.

**Table 2 Tab2:** The clinical symptom assessment scale

Item	Symptoms Assessment rating scale			
	0 (none)	1 (mild)	2 (moderate)	3 (severe)
Cough	No	Intermittent cough during the day does not affect work and life	Cough during the day or occasionally cough at night, slightly affecting work	Frequent cough, affecting work and rest
Cough sound	No	Low coughing sound	Weak coughing sound	Weak and low coughing sound
Expectoration	No	Sputum volume:10-50 ml	Sputum volume:51-100 ml	Day and night expectoration, Sputum volume > 100 ml
Dyspnea (difficulty breathing)	No	Difficulty breathing when walking or walking upstairs	Difficulty breathing with slight movement	Difficulty breathing occurs at rest
Pant	No	Occasional, does not affect work and life	Visible day and night, slightly affecting work	Can’t lay down, affecting sleep and activity
Mental weariness	No	in low spirits	mental fatigue	spiritual malaise
Fatigue	No	Feeling tired when labor	Feeling tired when moving	Getting tired even if not moving
Lack of qi and no desire to speak	No	Lack of qi, and don’t like talking too much	Lack of qi, and not enthusiastic about talking	Have no strength, don't even want to speak
Sleep disturbance	NO	easy to wake up and wake up early in the morning, but does not affect normal work	sleep less than 6 h per day, difficult to maintain normal work	sleep less than 4 h a day, difficult to maintain normal work

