## Method

### Study design

This is a prospective, multicentre, double-blind, randomized controlled trial to evaluate the efficacy and safety of YPF granules in improving the clinical symptoms of stable COPD and to explore the underlying mechanism. Based on the exclusion and inclusion criteria, a total of 316 eligible subjects will be enrolled and randomly assigned to the YPF treatment group or control group in a 1:1 ratio. The study flowchart is shown in Fig. 1. Following informed consent and collection of baseline information, treatment will be administered for 52 weeks according to stratified block randomization. All subjects will return to the hospital once on day 0 and at weeks 4,12,24,36, and 52 to complete the assessment of their symptoms, signs, and quality of life scores (assessed by CAT, SGRQ, laboratory indicators, etc.). If subjects have an acute exacerbation, an additional visit will be made on the first day of the exacerbation or as conditions permit. The specific assessments at each visit are detailed in Table 1.

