### Sample size

According to the results of the previous study [15], the mean difference in CAT scores between the YPF group and the control group was 2.2, and the combined standard deviation was 6.2184. The sample size was calculated accordingly, with an α risk of 0.05 and a β risk of 0.2 in a two-sided contrast. This study required a minimum of 252 subjects. Allowing for 20% attrition, a total sample size of 316 subjects was required, 158 in the treatment group and 158 in the control group.

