### Withdrawal and discontinuation criteria

All eligible patients have the right to withdraw from the trial at any time. During the trial, the following situations should be treated as withdrawals:Serious complications, significant physiological changes, serious adverse events, and other serious events that occur during the trial.Poor subject compliance of subjects (such as taking drugs in violation of the prescribed dose)Subjects are unwilling to continue the trial and ask to withdraw from the trialRefusal to accept medication or examination and lose of visitors.Subjects become unblinded halfway through the trial.

The reasons for subjects’ withdrawal or discontinuation from the trial should be documented in detail. For those who withdrawn from the trial because of adverse events, the investigators should take appropriate treatment measures according to the subject’s actual situation, and try to complete the last test for subsequent statistical analysis.

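### The only rule for collecting data from patients who leave covers adverse-event leavers alone, and it is not reconciled with a primary endpoint that needs a week-52 CAT score

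*Protocol article*

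**What the plan says.** - **Endpoint** (Protocol article, Efficacy indicators): for each arm, "the differences between the total CAT score at week 52 and baseline will be calculated", and the arms are then compared. No other time point defines the primary outcome.
- **Expected loss** (Sample size): "This study required a minimum of 252 subjects", and then "Allowing for 20% attrition, a total sample size of 316 subjects was required".
- **Leavers** (Withdrawal and discontinuation criteria): five situations count as withdrawal from the trial. They are serious events or complications, poor compliance, the patient's own request, refusal or loss to follow-up, and unblinding during the trial. Reasons are documented for everyone. For those who leave because of adverse events, and only for them, investigators are to "try to complete the last test for subsequent statistical analysis".
- **Schedule** (Table 1): CAT is measured at day 0, at weeks 4, 12, 24, 36 and 52, and at additional visits for exacerbations.
- **Analysis** (Statistical analysis; Efficacy analysis): efficacy is analysed in a full analysis set (FAS) and a per-protocol set. Changes in CAT are assigned to the log-rank test and the Cox model.

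**The concern.** The endpoint needs a week-52 score. The protocol expects about a fifth of patients not to supply usable data, and the shown text makes no provision for measuring leavers at week 52. The one collection rule it gives depends on why the patient left. A patient who leaves after an adverse event may have a final assessment. One who leaves for poor compliance, by request or after unblinding is not asked for one. The rule sends the result to the statistical analysis but names neither the test nor the week it is to represent.

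The trial's own text makes outcome-related loss plausible. Every participant has had at least two moderate exacerbations or one severe exacerbation in the past year (Inclusion criteria). Serious events count as withdrawal. The Background reports a 32.3% lower exacerbation risk on YPF in the previous trial. If that effect recurs, withdrawals linked to exacerbations could be more frequent on placebo. At stake are how far the week-52 contrast represents the randomised arms, and whether the data needed to check this will exist.

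The stated method does not help. Log-rank and Cox are methods for times to an event and do not suit a change in a score. They also give no week-52 mean difference, which is the quantity used to size the trial.

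**Working it through.** **1. Reproduce the plan's figure.** Inputs from Sample size: "the mean difference in CAT scores between the YPF group and the control group was 2.2"; "the combined standard deviation was 6.2184"; "with an α risk of 0.05 and a β risk of 0.2 in a two-sided contrast". Allocation from Study design: "randomly assigned to the YPF treatment group or control group in a 1:1 ratio".

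n per arm = 2(z₀.₉₇₅ + z₀.₈₀)² × SD² / difference² = 2 × (1.960 + 0.8416)² × 6.2184² / 2.2² = 2 × 7.849 × 38.668 / 4.84 = 125.4, so 126 per arm and 252 in total. Inflation: 126 / 0.8 = 157.5, so 158 per arm and 316 in total. The plan's figures are correct.

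**2. Expected leavers.** 0.20 × 316 = 63.2, or 31.6 per arm. That leaves 252.8 patients, which matches the 252 required.

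**3. Final assessment by reason for leaving** (Withdrawal and discontinuation criteria).

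| Reason | Counts as withdrawal | Final test requested |
|---|---|---|
| Adverse event | yes | yes, content unnamed |
| Poor compliance | yes | not stated |
| Own request | yes | not stated |
| Refusal or loss | yes | not stated |
| Unblinded | yes | not stated |

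All leavers will still have the scheduled CAT scores taken before they left.

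**4. Bias if only patients with a week-52 score were compared.** Assume that leavers would have scored g points worse than completers in both arms, with dropout d_P on placebo and d_Y on YPF. If the difference in all randomised patients is 2.2, the completer difference is 2.2 − (d_P − d_Y) × g. The values of g and the dropout splits are assumptions.

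| d_Y | d_P | g = 2 | g = 4 |
|---|---|---|---|
| 20% | 20% | 2.2 | 2.2 |
| 15% | 25% | 2.0 | 1.8 |
| 25% | 15% | 2.4 | 2.6 |
| 10% | 30% | 1.8 | 1.4 |

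**5. What the undefined last test could do.** Suppose a share f of leavers contributed an early value as if it were week 52. Each arm then has 126.4 + 31.6f values. If the early values carry no treatment effect, the expected difference is 126.4 × 2.2 / (126.4 + 31.6f).

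| f | Values added per arm | Difference, no effect in early values | Power, no effect | Power, full 2.2 effect |
|---|---|---|---|---|
| 10% | 3.2 | 2.15 | 79% | 81% |
| 25% | 7.9 | 2.07 | 78% | 83% |
| 50% | 15.8 | 1.96 | 76% | 85% |

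**6. Gain from using all scheduled CAT values.** This was simulated with 158 per arm, a difference of 2.2, SD 6.2184 and 20% loss (3,000 trials in each of 12 scenarios). Assumptions: adjacent-visit correlation 0.6 to 0.8; dropout unrelated to the last CAT, or rising with it at a log-odds of 0.7 or 1.2 per SD.

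- Completer t-test: estimate 2.22 down to 2.01, power 81% down to 74%.
- Likelihood-based repeated-measures estimate: 2.18 to 2.22, power 78% to 85%, about 2 to 8 points above the completer test in matched scenarios.

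Dropout here depends on observed CAT, which favours the repeated-measures estimate by construction.

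**The case against.** The strongest reply is that this is a missing-data complaint against an article. The FAS definition and the missing-data method are commonly left to the full protocol or the SAP, so their absence is no defect. That stands, and the point does not rest on it.

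A reader might also infer that the comparison will consist of completers plus a few early values standing in for week 52. The documents do not support this:

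- An FAS is named beside the per-protocol set, which points away from a completers-only analysis.
- No section enters the last test as the week-52 value. The sentence concerns adverse-event leavers, and the test may be a safety test rather than CAT.
- Dividing by 0.8 is routine inflation and is compatible with a mixed model. The 20% is an allowance, not a decision to exclude those patients.
- Changes in CAT are also listed as a secondary outcome, so the interim scores cannot be said to be discarded.

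The completer t-test in the simulation is not the method the protocol names for CAT change either. Those power figures show what the scheduled data could add; they do not describe the stated plan.

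Two things survive. Who is measured at withdrawal is fixed by the protocol, and an SAP cannot recover scores that were never requested. And the analysis stated for CAT change is one the article does fix, and it does not fit the endpoint.

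**Conclusion.** The point holds in a limited form. The withdrawal section requests a final test from one class of leaver only, leaves its content open, and does not relate it to an endpoint fixed at week 52. The two sections must be reconciled. The sample size is correct and needs no change.

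The size is uncertain because no dropout split or leaver deficit is given. On the completer comparison the bias is nil if both are equal between arms. It is 0.2 to 0.4 points in either direction at 15% versus 25% dropout. At 10% on YPF and 30% on placebo, the difference is understated by 0.4 to 0.8 points. All of these assume leavers 2 to 4 CAT points worse. The change is worth making because it is cheap and because uncollected scores cannot be restored; a large bias has not been shown.

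**What to change.** 1. **Withdrawal and discontinuation criteria.** Ask for a CAT at withdrawal from every leaver, whatever the reason. Record it at the week it was taken and never carry it forward as the week-52 value. Say what the last test comprises. This concerns data collection only and leaves the withdrawal criteria themselves as they are.
2. **Efficacy indicators and Efficacy analysis.** Replace log-rank and Cox for CAT change with a repeated-measures mixed model in the FAS on CAT at weeks 4, 12, 24, 36 and 52. Include arm, visit, arm-by-visit, baseline CAT and eosinophil stratum, and report the week-52 contrast as the primary result.
3. **Sensitivity.** Add one analysis that allows dropout to depend on unobserved CAT values, for example with leavers following the placebo course.

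Cost: protocol and SAP wording, some programming, and one short questionnaire at withdrawal. No extra patients or scheduled visits are needed. The model assumes that dropout is explained by observed data (missing at random), and the sensitivity analysis tests that assumption.

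### The log-rank/Cox method named for CAT change does not estimate the primary contrast; a linear model with baseline CAT and the eosinophil stratum would, at no extra data cost

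*Protocol article*

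**What the plan says.** Five places in the protocol article bear on this point.

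- **Outcome measurements, Efficacy indicators.** The primary outcome is the change in total CAT score at week 52: "the differences between the total CAT score at week 52 and baseline will be calculated respectively for the experimental and the control groups". The two groups are then compared on that difference. No test or model is named here.
- **Efficacy analysis.** Methods are assigned endpoint by endpoint. Changes in CAT, SGRQ, total symptom score and single symptom scores are given the log-rank test and the Cox proportional-hazards model. No baseline value and no stratum is mentioned.
- **Randomization, blinding and unblinding.** "the absolute value of eosinophils in peripheral blood at the time of enrollment is taken as the stratification factor", with a cut-off of 0.3 × 10^9/L.
- **Subgroup analyses.** This is the only analysis section that uses the eosinophil factor, for a stratified analysis of the efficacy indicators.
- **Sample size.** "the mean difference in CAT scores between the YPF group and the control group was 2.2" and "the combined standard deviation was 6.2184", "with an α risk of 0.05 and a β risk of 0.2 in a two-sided contrast". From these: "This study required a minimum of 252 subjects", and "Allowing for 20% attrition, a total sample size of 316 subjects was required".

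**The concern.** The outcome definition and the sample size both concern a difference between two means. The method named for CAT change concerns hazards. For a score change the article defines neither an event nor a time to it. If the change itself were put in place of time, Cox regression would use only the ranking of the changes and return a hazard ratio on the CAT scale. Either way the result is not a difference in CAT points that can be set against the planned 2.2.

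The method sentence therefore has to be rewritten, and the choice of its replacement matters. CAT is measured on day 0 in all subjects (Table 1), and the eosinophil stratum is known at randomisation. The article itself expects eosinophil phenotype to bear on response (Background and Discussion). A replacement that left both out would give up precision that costs nothing to obtain.

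The Sample size section adds an ambiguity. It speaks of CAT scores where the endpoint is a change, so a reader cannot tell which quantity the SD describes.

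**Working it through.** **Inputs from the article.** Difference 2.2; SD 6.2184; two-sided α 0.05; power 0.80; 1:1 allocation; 252 evaluable (126 per arm); 20% attrition; 316 in total.

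**Assumed, because not given.** The correlation r between baseline and week-52 CAT, taken over 0.3 to 0.8, and equal CAT variance at the two times.

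**Step 1: reproduce the stated size.** For two means, n per arm = 2(1.960 + 0.842)² × 6.2184² / 2.2² = 125.4, rounded up to 126, so 252. Then 126/0.8 = 157.5, rounded up to 158 per arm, so 316. Both stated figures reproduce. The standard error at 126 per arm is 6.2184 × √(2/126) = 0.783, and 2.2/0.783 = 2.808, which gives 80.2% power by the normal approximation (79.9% by the noncentral t). The trial is thus sized for an unadjusted comparison of two means, not for a log-rank test.

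**Step 2: effect of baseline adjustment.** Let σ be the SD of a score at one time point.

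- Variance of the change: 2σ²(1 − r)
- Residual variance after adjusting for baseline: σ²(1 − r²)
- Ratio: (1 − r²) / [2(1 − r)] = (1 + r)/2

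The ratio is 0.65, 0.75, 0.85 and 0.90 at r = 0.3, 0.5, 0.7 and 0.8. It is below 1 for every r below 1, whichever quantity 6.2184 describes.

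**Step 3: power at 126 per arm (normal approximation).**

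If 6.2184 is the SD of the change, the adjusted SD is 6.2184 × √((1 + r)/2):

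| r | Unadjusted power | Adjusted SD | Adjusted power | Evaluable total for 80%, adjusted |
|---|---|---|---|---|
| 0.3 | 80.2% | 5.013 | 93.6% | 164 |
| 0.5 | 80.2% | 5.385 | 90.0% | 190 |
| 0.7 | 80.2% | 5.733 | 86.1% | 214 |
| 0.8 | 80.2% | 5.899 | 84.1% | 226 |

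If 6.2184 is the SD of a score at one time point:

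| r | SD of change | Unadjusted power | Adjusted SD | Adjusted power |
|---|---|---|---|---|
| 0.3 | 7.358 | 66.0% | 5.932 | 83.7% |
| 0.4 | 6.812 | 72.7% | 5.699 | 86.5% |
| 0.5 | 6.218 | 80.2% | 5.385 | 90.0% |
| 0.7 | 4.817 | 95.2% | 4.441 | 97.6% |
| 0.8 | 3.933 | 99.3% | 3.731 | 99.7% |

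The two readings coincide at r = 0.5, because 2(1 − 0.5) = 1.

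**Step 4: what cannot be sized.** These figures describe a comparison of mean changes, which is what the endpoint and the sample size imply. They do not describe a log-rank test on score changes. The further gain from including the eosinophil stratum cannot be computed, since the article gives neither its prevalence nor its relation to CAT.

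**The case against.** The strongest reply is that a journal article condenses the full protocol, and that covariates are commonly left to the analysis plan, which is not shown. This stands as far as silence goes. The sentence defining the primary outcome fixes an endpoint and a contrast; it names no model and rules out no covariate. A reader might infer from it that the sponsor has committed to an unadjusted change-score test. The text does not support that inference. The Efficacy analysis section is not silent, though. It names a method for CAT change, and that method does not deliver the contrast in the outcome definition.

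A second reply is that an unadjusted comparison of changes is valid in a randomised trial. That is correct. Chance imbalance in baseline CAT is a matter of precision, not of bias across randomisations.

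A third stronger reading is that the 80% power rests on an unstated correlation, or that the trial is underpowered. The article does not support that either. If 6.2184 is the SD of the change, 80% holds at any r. If it is a single-time-point SD, power is lower than planned only for r below about 0.5 and higher above it. The article does not say which SD it is.

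Finally, the Subgroup analyses section could be read as a stratified overall analysis. Its heading, and the Discussion's aim of exploring whether efficacy differs between eosinophilic and non-eosinophilic phenotypes, point to subgroup results instead.

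**Conclusion.** The point holds in two parts and should be acted on.

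First, the method named for CAT change does not match the primary contrast or the sample size calculation. This rests on the text alone and needs no assumption.

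Second, the natural replacement is a linear model with baseline CAT and eosinophil stratum. The gain from baseline adjustment depends on the assumed r and on equal variances: the variance falls by 35% at r = 0.3, 25% at 0.5 and 10% at 0.8. At r = 0.5, power at 126 per arm rises from 80% to about 90%, or equivalently about 190 evaluable subjects would do the work of 252. This is an efficiency gain, not the repair of a biased analysis.

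The unlabelled SD is a smaller, conditional matter. The stated 252 and 316 are arithmetically correct on their inputs, and no shortfall in power is shown.

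**What to change.** 1. In Efficacy analysis, replace the log-rank test and Cox model for CAT change with a linear model (ANCOVA or a repeated-measures equivalent) of week-52 change on treatment, baseline CAT and eosinophil stratum (cut-off 0.3 × 10^9/L). Report the adjusted difference in CAT points with its 95% confidence interval.
2. Do the same for SGRQ, the total symptom score and the single symptom scores, each with its own baseline. The existing log-rank/Cox wording must be removed for these endpoints; otherwise two conflicting methods would stand side by side.
3. In Sample size, state whether 2.2 and 6.2184 refer to the change or to a score at one time point. If the latter, give the baseline to week-52 correlation from the previous study and restate the power.

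The cost is a rewritten method sentence and a clarified sample size sentence. No extra subjects, visits or measurements are needed, because Table 1 already schedules CAT, SGRQ and the symptom scale on day 0 and at every follow-up visit. The change should be documented before the data are unblinded.

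### The annualized exacerbation rate is defined per head rather than per person-year, and both admission rates share that denominator, so with incomplete follow-up the rates are too low and unequal withdrawal can distort the comparison

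*Protocol article*

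**What the plan says.** In the protocol article, Outcome measurements, Efficacy indicators, the first secondary outcome is named "Annualized rates of moderate or severe COPD exacerbations" and is defined as "the number of acute exacerbations of moderate or severe COPD during 52-week treatment/total participants in the group". The next item gives the two admission rates the same form: "All-cause admission rate = (total number of admission during 52-week treatment)/ (total number of participants in the group", and for exacerbation admissions "number of admission due to acute exacerbation during 52-week treatment)/ (total number of participants in the group". The admission rates do not carry the annualized label. A later item, exacerbation rates by severity, carries the label but restates no formula. Time at risk enters none of the three formulas.

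On completeness of follow-up, Sample size says "Allowing for 20% attrition, a total sample size of 316 subjects was required". Withdrawal and discontinuation criteria counts as withdrawals, among other reasons, "Serious complications, significant physiological changes, serious adverse events, and other serious events that occur during the trial". For withdrawals due to adverse events it asks investigators to "try to complete the last test for subsequent statistical analysis". It says nothing about recording exacerbations or admissions between withdrawal and week 52.

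Statistical analysis, Efficacy analysis, treats these rates as categorical and assigns them to Fisher's exact test. No exposure term appears.

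**The concern.** Events per head equal events per year only if every subject is observed for the full 52 weeks, and the protocol plans on the basis that some will not be. If events after withdrawal are not recorded, the numerator stops at withdrawal while the denominator still credits a whole year. The reported figure is then not an annualized rate, and it cannot be compared with person-time rates from other trials.

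The comparison between arms is also exposed. If one arm loses more subjects, or loses them earlier, its rate falls further for that reason alone. Fewer exacerbations is the benefit that the Background section already claims for this product (a 32.3% lower risk in the earlier trial), so these secondary results are likely to be read closely.

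**Working it through.** **Inputs from the protocol article.** Head-count denominators (Efficacy indicators); 20% attrition, a CAT difference of 2.2, SD 6.2184, two-sided α 0.05, β 0.2, and 158 per arm (Sample size); 52 weeks of planned treatment.

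**Inputs assumed, because the article does not give them.** A constant event rate; no events counted after withdrawal; those who withdraw observed on average for a share f of the year, with f = 25%, 50% or 75%; and several splits of withdrawal between the arms.

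**The protocol's own figure.** n per arm = 2(1.96 + 0.8416)² × 6.2184² / 2.2² = 125.4, rounded up to 126, so 252 in total. Dividing by 0.8 gives 126 / 0.8 = 157.5, rounded up to 158 per arm, so 316. Both stated numbers reproduce. They concern the CAT score only; no power is stated for the exacerbation or admission rates.

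**Step 1, a single rate.** With a share d withdrawing, observed time per subject is 1 − d(1 − f) years, so

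head-count rate / true annual rate = 1 − d(1 − f).

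At d = 0.20:
- f = 25%: 1 − 0.20 × 0.75 = 0.85
- f = 50%: 1 − 0.20 × 0.50 = 0.90
- f = 75%: 1 − 0.20 × 0.25 = 0.95

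Each rate is understated by 5-15%, and by 10% at the midpoint.

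**Step 2, the rate ratio when there is no true effect.** Apparent ratio = [1 − d_YPF(1 − f)] / [1 − d_placebo(1 − f)].

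| Withdrawal, YPF vs placebo (assumed) | f = 25% | f = 50% | f = 75% |
|---|---|---|---|
| 20% vs 20% | 1.000 | 1.000 | 1.000 |
| 25% vs 15% | 0.8125/0.8875 = 0.915 | 0.875/0.925 = 0.946 | 0.9375/0.9625 = 0.974 |
| 30% vs 10% | 0.775/0.925 = 0.838 | 0.85/0.95 = 0.895 | 0.925/0.975 = 0.949 |
| 15% vs 25% | 0.8875/0.8125 = 1.092 | 0.925/0.875 = 1.057 | 0.9625/0.9375 = 1.027 |

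**Step 3, false-positive rate.** This was simulated with 158 per arm, 10,000 runs, an assumed true rate of 1 per year, dispersion 0.5 and uniform withdrawal times. Arms were compared by a two-sided 5% test on the log rate ratio. This is not the Fisher's exact test that the article names.

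| YPF vs placebo | Head-count: mean ratio, type I error | Person-years: mean ratio, type I error |
|---|---|---|
| 20% vs 20% | 1.00, 0.051 | 1.00, 0.050 |
| 25% vs 15% | 0.947, 0.065 | 1.00, 0.051 |
| 30% vs 10% | 0.895, 0.116 | 1.00, 0.052 |

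In this simulation withdrawal is unrelated to event risk, which is the condition under which person-years remove the distortion.

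**The case against.** The strongest reply is that the harm is conditional and modest. Nothing in the article suggests that the arms will differ in withdrawal. The trial is double-blind with a matched placebo, good safety is reported from the earlier study, and the 20% is one overall allowance made for the CAT sample size. With equal withdrawal the ratio is undistorted. Under the simulation's assumptions the standard error of the log rate ratio is about √(2 × 1.5/158) = 0.14, so ratios of 0.946 and 0.895 lie only about 0.4 and 0.8 standard errors from no effect. The outcomes are secondary, and time to first exacerbation, also listed, can accommodate censoring.

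This stands as a limit on size. It does not rescue the definition: the absolute rates are still too low when withdrawal is balanced, and time to first event does not replace a rate of recurrent events.

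Three stronger readings should be resisted:
- A reader might infer that someone who leaves at week 8 is counted as event-free for the year. The numerator includes that subject's events up to withdrawal; only the remaining weeks are wrongly treated as event-free.
- A reader might infer that the formula favours YPF. The direction depends on which arm loses more follow-up, and the article does not indicate one.
- A reader might infer that the admission rates are mislabelled as well. They are not called annualized, so for them the problem is incomplete follow-up alone.

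The article also does not say outright that events after withdrawal go unrecorded. It states no such collection, and the understatement depends on that premise.

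**Conclusion.** The point holds as a definition that does not match its label for the exacerbation rate, and as an unsuitable denominator for all three stated rates. The formula is written out, so this is not a detail left to an analysis plan.

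At the protocol's own 20% attrition the understatement is 5-15%, given constant event rates, no events counted after withdrawal, and those who withdraw observed for 25-75% of the year on average. A false difference between arms arises only if the amount or timing of withdrawal differs between them. In the assumed scenarios the ratio under no effect runs from 0.838 to 0.974 when YPF loses more and from 1.027 to 1.092 when placebo loses more. Confidence is high for the mismatch between label and formula. The distortion of the treatment comparison is a possibility, not a prediction. The correction should be made, but it concerns secondary outcomes only.

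**What to change.** Define each exacerbation rate, overall and by severity, and both admission rates as total events divided by total person-years of observed follow-up, from randomisation to week 52, death or last contact, whichever comes first. Compare the arms with a count model, for example negative binomial, with log follow-up time as an offset. This has to replace the Fisher's exact test now named for these rates, because that test cannot use event counts or exposure; changing the definition alone would leave an analysis that does not estimate the rate.

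State that the person-time estimate is unbiased only if withdrawal is unrelated to exacerbation risk. That needs saying because serious events are themselves listed as withdrawals. Recording exacerbations and admissions to week 52 in subjects who have withdrawn, where they agree, would reduce reliance on this assumption, but it is an addition to data collection and should be decided separately.

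The cost is a small change to definition and analysis. Table 1 records the start of treatment, and exacerbations and hospitalizations at each follow-up visit, so follow-up time should be derivable from treatment start and the last visit or contact. The article requires the reason for withdrawal to be documented but does not mention its date, so the case report form should be checked for that. The primary outcome and the sample size of 316 do not change.
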